## Abstract

**Background:**

Postoperative pain is common after nasal endoscopic surgery. It interferes with the quality of sleep and delays postoperative recovery. Acupuncture is an effective tool for pain management. However, electroacupuncture specifically for the relief of postoperative pain after nasal endoscopic surgery has not yet been studied in a randomized controlled trial.

**Methods/design:**

This randomized sham-controlled patient- and assessor-blind pilot trial has been designed to evaluate the efficacy and safety of electroacupuncture in managing postoperative pain following nasal endoscopic surgery to treat sinusitis due to nasal polyps. Altogether, 30 participants will be randomly allocated to an electroacupuncture or non-invasive sham control in a 1:1 ratio. Treatment will occur within 2 h before the operation, immediately after the operation upon arrival in the recovery ward, and once daily for 3 days. The primary outcome is the pain numerical rating scale, which will be analyzed using the area under the curve. The secondary outcome measures include heart rate and blood pressure after the operation, sleep quality during the hospital stay (actigraph), quality of recovery, and the 36-item short form health survey. This trial will use an intention-to-treat analysis.

**Discussion:**

This pilot randomized controlled trial will explore the feasibility of the further clinical application of electroacupuncture for the management of postoperative pain. It will inform the design of a further full-scale trial.

**Trial registration:**

Chinese Clinical Trial Registry, ChiCTR1900024183. Registered on 29 June 2019.

## Background

Postoperative pain is an important symptom following nasal endoscopic surgery for sinusitis due to nasal polyps. Effective management of postoperative pain after nasal endoscopic surgery is especially important for patient recovery. Pain due to a nasal filling may interfere with breathing, sleep quality, and patient satisfaction. According to previous reports, a failure to treat acute pain immediately may cause long-term chronic pain [1, 2]. The effective relief of acute pain is a challenge for patients and physicians following nasal endoscopy. Analgesic drugs, especially opioid analgesics, are often used to relieve pain after surgery. However, there are risks due to side effects, such as respiratory depression and drowsiness, which can lead to a delayed postoperative recovery. Thus, a safe and effective way to control postoperative pain and reduce recovery times needs to be identified.

Acupuncture has been widely used for pain relief, and its analgesic effects have been reported worldwide. Several studies have shown that acupuncture can relieve pain after surgery, including oral surgery [3, 4], cardiac surgery [5], laparoscopic cholecystectomy [6–8], gynecological surgery [9, 10], back surgery [11], and nasal surgery [12]. Therefore, acupuncture may relieve postoperative pain following nasal endoscopic surgery. Despite the positive results of these previously published studies, the results are not dependable due to issues such as small sample sizes, inadequate randomization, and lack of blinding. Therefore, high-quality evidence is needed to confirm the previous findings and for a protocol to be developed for the use of acupuncture for postoperative pain.

For those reasons, we designed a randomized controlled trial (RCT) using appropriate randomization, rigorous concealment of allocation, and blinding to examine the efficacy of electroacupuncture (EA) in relieving postoperative pain after nasal endoscopy. We aim to determine: (1) whether EA is useful for relieving postoperative pain after nasal endoscopy and (2) whether it can reduce postoperative recovery times. This study may provide high-quality evidence to support a standard protocol for the clinical application of EA for treating postoperative pain after nasal endoscopic surgery.

We hypothesize that EA is effective, safe, and feasible for postoperative pain management after nasal endoscopic surgery.

## Methods/design

### Study design

This is a single-site patient- and assessor-blinded placebo-controlled pilot RCT. It will be carried out in Shanghai Municipal Hospital of Traditional Chinese Medicine. Eligible patients will be randomly assigned to the EA group or the sham electroacupuncture (SEA) group in a 1:1 allocation ratio. All patients must sign the informed consent form before being enrolled in the trial. A flowchart of the study process is detailed in Fig. 1. Additional file 1 contains the completed Spirit checklist.

**Fig. 1 Fig1:**
[figure not shown]
Flowchart for this study. EA electroacupuncture, QoR-15 15-item Quality of Recovery Scale, SF-36 36-item Short Form Health Survey

### Sample size

This is a pilot study. In the relevant literature, there are no previous studies utilizing the same evaluation method as the primary outcome to compare a sham acupuncture control. Therefore, we were unable to calculate the statistical power formally. The appropriate sample size for a two-arm pilot study should be more than 12. We assumed a 20% dropout rate, so that we will recruit 15 participants into each group. We will, therefore, recruit a total of 30 individuals for this RCT [13–15].

### Recruitment

Patients will be recruited to this RCT in Shanghai Municipal Hospital of Traditional Chinese Medicine. Eligible subjects who have been scheduled for nasal endoscopic surgery for sinusitis due to nasal polyps will be invited to participate. They will be referred from an otorhinolaryngologist. A research assistant will screen them and obtain written informed consent. They will then be randomly allocated to either the EA group or the SEA group. The schedule of enrolment, intervention, and assessments is detailed in Table 1.

**Table 1 Tab1:** Schedule of enrolment, intervention, and assessments

	S	B	O	Preoperative period	Postoperative period		
Timepoint				Within 2 h before operation	Upon recovery	Hourly for 6 h after surgery	Once daily until discharge
Basic information							
Informed consent	X						
Inclusion/exclusion	X	X					
Medical history	X						
Vital signs	X	X	X	X	X	X	X
Interventions							
EA				X	X		X
Sham EA				X	X		X
Assessments							
Primary outcome							
NRS					X	X	X
Secondary outcomes							
HR and BP			X	X	X	X	X
Actigraphy		X	X				X
QoR-15					X		X^*^
SF-36					X		X^*^
Others							
Adverse events			X	X	X	X	X
Patient satisfaction							X
Success of blinding							X

*EA* electroacupuncture, *S* screening, *B* baseline, *O* operation, *NRS* numerical rating scale, *HR* heart rate, *BP* blood pressure, *QoR-15* 15-item Quality of Recovery Scale, *SF-36* 36-item Short From health survey

* On day of discharge

#### Inclusion criteria

Patients who meet all of the following criteria can be included:
American Society of Anesthesiologists physical status I to IIEligible for nasal endoscopic surgery for sinusitis due to nasal polypsAged 18–60 yearsCapable of understanding the trial and providing responses about the outcome measurementAgree to participate in the survey and sign a written informed consent form

#### Exclusion criteria

Patients who meet any of the following criteria will be excluded:
Having chronic pain currently requiring treatment by an opioid or nonsteroidal anti-inflammatory drugHaving a severe psychiatric disease or cognitive impairment and not able to understand the trialHaving hepatitis B, hepatitis C, HIV infection, or syphilisHaving a history of alcohol or drug abuseHaving any local or systemic infectionHistory of acupuncture treatment in the past 6 months

### Randomization and allocation concealment

A random sequence will be produced by block randomization using the software SPSS version 23.0 by an independent research assistant. After the participants have completed the screening process and baseline assessment, they will be randomly assigned to one of the groups in a 1:1 ratio using random numbers in opaque envelopes. The treatment allocation codes will not be revealed before the first treatment. In an effort to minimize breaks in coding, the principal investigator who designed the trial and the research personnel who perform the outcome assessments will also be blinded to the treatment assignment.

Before the beginning of treatment, we will tell the participants that they have the same probability of being assigned to the EA group or the SEA group. To ensure that participants remain blinded, they will wear an eye mask during treatment. Only the acupuncturist who performs the treatment will know the group allocation at the time of treatment. The principal investigator, the data analysts, the outcome assessors, and statistician will remain blinded.

### Intervention protocol

All participants will be asked to fast from 8 h before the operation. They will undergo a standard operative procedure and receive postoperative treatment. Participants will be transferred to the ward within 30 min after the operation. EA or SEA will be given within 2 h prior to the surgery, immediately after surgery on arrival in the recovery ward, and daily following surgery for 3 days (five treatment sessions in total). If a participant drops out before completing the study, the reason will be recorded.

The acupuncture methods are described in Table 2. In each treatment session, the patients will be in a private area and placed in the supine position. They will wear an eye mask to prevent them from observing the treatment procedure. The researcher will sterilize the patient’s skin with 75% alcohol wipes before treatment. Each treatment session will last for 30 min. When the needles are removed, the researcher will use a clean piece of cotton wool to prevent bleeding by compressing the points. In the first treatment, 11 acupoints will be used and 17 acupoints will be used in the subsequent postoperative treatments. The acupoints and rationale are summarized in Table 3.

**Table 2 Tab2:** Treatment methods of electroacupuncture and acupoints

	EA group	SEA group
Acupoints	All sessions: LI4, PC6, HT7, LI20, ST36, GV23 Postoperatively: GV20, GV29, EX-HN22, SP6	All sessions: LI4, PC6, HT7, LI20, ST36, GV23 Postoperatively: GV20, GV29, EX-HN22, SP6
Depth of insertion	10 mm: HT7, GV20, GV23, GV29, LI4, LR3	No insertion
	30 mm: LI20, SP6, PC6, ST36	
Needle type	Steel needles (Wuxi Jiajian Medical Co. Ltd. Wuxi, China)	Blunt needles (Streitberger placebo needle)
Needle sensation	With *de-qi* sensation	Without *de-qi* sensation
Electric stimulation	Three pairs of needles: LI4–ST36 (bilaterally), GV20–GV23 Connected to an electric stimulator (HANS-200B) Deliver continuous wave-type mid-frequency (15Hz) current of 2 mA	Three pairs of needles: LI4–ST36 (bilaterally), GV20–GV23 Connected to an electric stimulator (HANS-200B) No electrical current delivered

*EA* electroacupuncture, *SEA* sham electroacupuncture

**Table 3 Tab3:** Acupoint selection and rationale based on traditional Chinese medicine

Acupoint	Location	Traditional Chinese medicine indication	Suggested technique
LI4 (*hegu*)	Dorsum of hand, at the level of the midpoint of the second metacarpal bone, between the first and second metacarpal bones	Alleviates nasal pain	Needle perpendicular, 0.5–1.0 *cun*
PC6 (*neiguan*)	Palmar aspect of the forearm, between the tendons, 2 *cun* away from the transverse crease of the wrist	Alleviates gastric pain and calms the *shen (spirit)*	Needle perpendicular, 0.5–1.5 *cun*
HT7 (*shenmen*)	Palmar aspect of the wrist, ulnar end of the transverse crease	Helps in calming the *shen* (spirit)	Needle perpendicular, 0.3–0.5 *cun*
LI20 (*yingxiang*)	0.5 *cun* lateral to the midpoint of the border of line ala nasi, in the nasolabial groove	Helps in nasal congestion and epistaxis.	Needle perpendicular, 0.3–0.5 *cun*
ST36 (*zusanli*)	Antero-lateral leg, 1 middle-finger breadth next to the anterior crest of tibia, 3 *cun* under the depression lateral to the patellar ligament	Helps in regulating *qi* and blood circulation	Needle perpendicular, 0.5–1.5 *cun*
GV23 (*shangxing*)	1 *cun* directly above the midpoint of the anterior hairline	Helps in rhinorrhea, epistaxis.	Needle perpendicular, 0.5–1.0 *cun*
GV20 (*baihui*)	5 *cun* directly above the midpoint of the anterior hairline, at the midpoint of the line connecting the apexes of the two auricles	Helps in calming the Shen (spirit)	Needle perpendicular, 0.5–0.8 *cun* Moxibustion can be used to reinforce the *yang*
GV29 (*yintang*)	On the forehead, at the midpoint between the two medial ends of the eyebrow	Helps in insomnia, dizziness; epistaxis, rhinorrhea.	Needle perpendicular, 0.3–0.5 *cun*
EX-HN22 (*anmian*)	On the napex, at the midpoint between TE17 and GB20	Helps in calming the Shen (spirit), improving insomnia.	Needle perpendicular, 0.8–1.2 *cun* Moxibustion can be used to reinforce the *yang*
SP6 (*sanyinjiao*)	Behind the medial tibia, 3 *cun* above the tip of the medial malleolus	Helps in regulating Qi and blood circulation improving insomnia, dizziness.	Needle perpendicular, 0.5–1.0 *cun*

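### Table 2 sets LI20 at 30 mm, but Table 3 gives it the same 0.3–0.5 cun as two points set at 10 mm; the depth row also lists LR3, which is not a trial point, and omits EX-HN22, which is

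*Protocol article*

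**What the plan says.** The Intervention protocol section of the protocol article refers to Table 2 for the acupuncture methods and to Table 3 for the points and their rationale.

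- **Points (Table 2), identical in both arms:** "All sessions: LI4, PC6, HT7, LI20, ST36, GV23 Postoperatively: GV20, GV29, EX-HN22, SP6".
- **Depths in the EA arm (Table 2), first line:** "10 mm: HT7, GV20, GV23, GV29, LI4, LR3".
- **Depths in the EA arm (Table 2), second line:** "30 mm: LI20, SP6, PC6, ST36". The sham arm has no insertion.
- **Suggested technique for LI20 (Table 3):** "Needle perpendicular, 0.3–0.5 *cun". The HT7 and GV29 rows give the same range.
- **Number of points:** "In the first treatment, 11 acupoints will be used and 17 acupoints will be used in the subsequent postoperative treatments".

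The section on the electroacupuncture group gives a needle length of 40 mm. It names the same ten points as Table 2, without LR3. The Quality control section makes needling depth one of the training topics.

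**The concern.** Two points with the 0.3–0.5 cun range are set at 10 mm, and a third with the same range is set at three times that depth. The third is LI20, which Table 3 places "0.5 *cun* lateral to the midpoint of the border of line ala nasi, in the nasolabial groove", next to the surgical field.

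Taken literally, Table 2 asks for three quarters of a 40 mm needle (30/40 = 75%) at that point. LI20 is used in every session, starting with the preoperative one: "EA or SEA will be given within 2 h prior to the surgery". Only EA patients would be exposed, because the sham needle does not enter the skin.

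Depth is also part of the EA dose. A pilot meant to inform a full-scale trial should leave one reproducible depth per point. With the two tables in conflict, the depth delivered at LI20 depends on which table the acupuncturist follows. LR3 and EX-HN22 are lesser list errors in the same row.

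**Working it through.** **Point counts.** LI4, PC6, HT7, LI20 and ST36 on both sides, plus GV23, give 5 × 2 + 1 = 11. The postoperative additions are GV20 (1), GV29 (1), EX-HN22 (2) and SP6 (2), which is 6, and 11 + 6 = 17. Both stated counts reproduce. They need EX-HN22 and leave no room for LR3. Comparing the depth row with the point list, LR3 is the only code with a depth that is not a trial point, and EX-HN22 is the only trial point without a depth.

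**Implied cun length.** The article gives no conversion, so the check divides each Table 2 depth by the two ends of the Table 3 range.

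| Point | Table 2, mm | Table 3, cun | Implied mm per cun |
|---|---|---|---|
| LI20 | 30 | 0.3–0.5 | 60–100 |
| HT7, GV29 | 10 | 0.3–0.5 | 20–33.3 |
| SP6 | 30 | 0.5–1.0 | 30–60 |
| LI4, GV23 | 10 | 0.5–1.0 | 10–20 |
| GV20 | 10 | 0.5–0.8 | 12.5–20 |
| PC6, ST36 | 30 | 0.5–1.5 | 20–60 |
| EX-HN22 | none | 0.8–1.2 | not available |
| LR3 | 10 | not listed | not available |

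**LI20.** The interval 60–100 does not meet 20–33.3, nor that of any other 10 mm point. It only touches the other 30 mm points, at their upper limit of 60. For both tables to hold, a cun at LI20 would have to be at least 60/33.3 = 1.8 times as long as at HT7 or GV29.

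**SP6.** The interval 30–60 does not meet the 10–20 of LI4 and GV23, which have the same Table 3 range. It does agree with HT7, GV29, PC6 and ST36 at 30–33.3 mm per cun. The conflict is therefore real, but it does not show whether SP6 or the LI4 and GV23 entries are wrong.

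**EX-HN22.** At the 20–33.3 mm per cun implied by HT7 and GV29, 0.8–1.2 cun runs from 16–24 mm to 26.6–40 mm. A depth of 30 mm falls inside the range from 30/1.2 = 25 mm per cun upward and outside it below that. The documents do not settle a value.

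**Extent.** There is one session before surgery, one on arrival in the recovery ward and three daily ones. Placements per EA patient who completes all five are 11 + 4 × 17 = 79. LI20 accounts for 2 × 5 = 10 (10/79 = 12.7%), or up to 15 × 10 = 150 in 15 EA patients. EX-HN22 and SP6 each account for 2 × 4 = 8 (10.1%). These are different kinds of problem and are not added together.

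**The case against.** Table 3's depths are headed as suggested technique, while the text names Table 2 as the description of the method. On that reading Table 2 already governs, and nine of the ten points have one depth in mm. Two points sharing a guidance range may also properly be needled to different depths. The acupuncturists are registered, hold a master's degree, have at least three years' experience and are trained on depth, so a literal 30 mm at LI20 may never be attempted. No one would needle LR3, since no point list contains it. EX-HN22 does have a range in Table 3, and a full protocol may give its depth in mm.

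Much of this stands. The documents show that the tables conflict, not which one is wrong. Training is a safeguard, and the placement counts measure neither harm nor bias. LR3 and EX-HN22 are minor.

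It does not remove the LI20 conflict. If Table 2 governs, the 30 mm is the operative instruction. If practitioners are expected to override it, the table needs correcting. The Table 3 entry specifies perpendicular insertion, so a slanted needle path is not the explanation. These are stated values that disagree, not detail left out of a condensed article.

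A reader might go further and infer a cun of 20 mm, the only length at which seven of the nine points with a depth in both tables agree, and then read off depths for EX-HN22 and SP6. The documents do not support that. They state no conversion, and the agreement at 20 mm arises only because the intervals meet at their endpoints: HT7, GV29, PC6 and ST36 at their minimum, and LI4, GV23 and GV20 at their maximum. At 30–33.3 mm per cun, SP6's 30 mm fits and LI4, GV23 and GV20 do not. LI20 fails at either length.

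**Conclusion.** The inconsistency holds for LI20 and should be resolved before treatment starts. The stated 30 mm is three times the depth given to the two points with the identical Table 3 range, and it concerns 10 of 79 placements per completing EA patient. The conclusion assumes only that a cun does not differ in length by a factor of 1.8 or more between LI20 and the other two points. It needs no outside conversion.

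LR3 and EX-HN22 are confirmed list errors in the same row. SP6 needs confirmation, but no replacement depth can be derived from the documents.

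A reader might also infer that EA patients will be injured or the pain comparison biased. The documents give nothing from which to estimate either. The point concerns delivery and reproducibility of the intervention, not sample size, error rates or the analysis.

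**What to change.** Before the first patient is treated:

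1. Move LI20 to the 10 mm row of Table 2, or have the clinical lead justify a deeper value and correct its Table 3 range to match.
2. Delete LR3 from the depth row.
3. Add a depth in mm for EX-HN22, set by the clinical lead in line with its 0.8–1.2 cun.
4. Have the clinical lead confirm SP6 against LI4 and GV23, and correct whichever entry is wrong.
5. Once LI20 is settled, and not before, state that the depths in mm in Table 2 apply where the tables differ.

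The cost is a few table cells and one sentence. The article describes the trial as still in preparation, and the change does not affect sample size, schedule or analysis.

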### The electroacupuncture group

The sterile disposable acupuncture needles are made of standard stainless steel (0.25 × 40 mm and 0.30 × 40 mm; Jia Jian, China). In all sessions, patients will receive treatment at 11 standard acupuncture points: bilateral *hegu* (LI4), *neiguan* (PC6), *shenmen* (HT7), *yingxiang* (LI20), *zusanli* (ST36), and *shangxing* (GV23). The postoperative treatment will be the same as the preoperative EA treatment, except that we will add the following six points: *baihui* (GV20), *yintang* (GV29), *anmian* (EX-HN22), and *sanyinjiao* (SP6). All acupoints were selected according to the acupuncture textbook of the International Standard Library of Chinese Medicine written by Zhang, Zhao, and Lao [17], the literature, and our clinical experience. The acupoints will be located with reference to the textbook. First the researcher will manipulate the needle manually until the patient reports needling sensations (*de-qi* sensation). An electric stimulator (HANS-200B) will be connected to three pairs of needles (LI4–ST36 bilaterally and GV20–GV23) to deliver a continuous wave-type low-frequency (2 Hz) current of 2 mA.

### Control group

In the control group, Streitberger placebo needles, a sham acupuncture device that has been widely reported and validated, will be used [18]. The non-invasive sham needles will be positioned 1.5 *cun* lateral and posterior to the true acupoints [19, 20]. The blunt tip of the sham needles will touch the surface of the skin but will not penetrate it. The electric stimulator (HANS-200B) will be beside the patients and three pairs of electrodes will be connected to LI4–ST36 (bilaterally) and GV20–GV23 for 30 min but no electrical current will be delivered.

### Outcome measures

The participant’s recovery will be monitored during and after the operation. The primary outcome is postoperative pain scores measured using a NRS. The secondary outcomes include heart rate (HR) and blood pressure (BP) after the operation, sleep quality during the hospital stay (actigraphy), quality of recovery, and overall health. In addition, the exact type of operation and when EA or SEA treatment is given will be recorded for analysis. If the participants cannot be managed according to the protocol for any reason, including side effects, no further data will be collected. The assessment schedule is detailed in Table 1.

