#### Primary outcome

NRS is a commonly used scale for assessing clinical pain. It is easier for patients to grade pain intensity with numbers rather than other measurements like the visual analog scale. The NRS is an 11-point scale for pain, with 0 indicating no pain and 10 indicating the worst possible pain. NRS pain scores will be assessed hourly for 6 h after surgery, then daily for 3 days [21, 22].

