### Safety assessment

Before signing the informed consent form, participants will be told about the potential adverse events related to acupuncture, such as bruises, hematomas, infection, and pain. Adverse events will be graded as 1 (mild), 2 (moderate), or 3 (severe or medically significant). Any adverse events that occur during the trial will be recorded by the patients and doctors. Vital signs will be assessed at the time of the event, including HR, BP, and respiratory rate. All details of adverse events will be reported in a case report form. If any severe adverse event occurs, we will terminate the EA or SEA treatment and the Clinical Research Center for Drugs of the Shanghai University of Traditional Chinese Medicine will unblind the participant to determine whether the serious adverse event is related to EA or SEA. A final decision will made on whether to continue the study. We will analyze the influence of all events at the end of the trial.

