### Statistical analysis

An independent statistician blinded to group allocation will perform the statistical analyses using the statistical software SPSS 23.0 for Windows. The analyses will include an intention-to-treat analysis incorporating data from any participants who have dropped out of the trial. We will use multiple imputation for missing data. All demographic and clinical characteristics of the subjects (such as sex, age, and weight) will be analyzed using descriptive statistics. We will identify the homogeneity of demographic characteristics and study variables between the two groups. Continuous variables will be reported as means ± standard deviations whereas qualitative data will be presented as frequencies and percentages. To analyze the primary outcome, the area under the curve of the NRS pain scores will be calculated using the trapezoidal method. Comparisons between groups will be made using Student’s *t*-test. The secondary outcomes—BP, HR, QoR-15, SF-36, and actigraphy assessments (total sleep time, sleep awakenings, and sleep efficiency)—will be compared between the two groups with Student’s *t*-test or the Wilcoxon rank-sum test. All reported *p* values will be two-sided, and *p* < 0.05 is considered statistically significant.

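### Ending data collection when a participant cannot be managed per protocol undermines the promised intention-to-treat analysis and puts the primary outcome at risk of informative missingness

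*Protocol article*

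**What the plan says.** The rule is in the protocol article, Outcome measures: "If the participants cannot be managed according to the protocol for any reason, including side effects, no further data will be collected".

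Three other parts of the article bear on it:

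- **Statistical analysis** promises that "The analyses will include an intention-to-treat analysis incorporating data from any participants who have dropped out of the trial", and adds: "We will use multiple imputation for missing data". The Abstract also commits the trial to intention-to-treat. The imputation model and its assumption are not stated.
- **Primary outcome and Statistical analysis** define what is at risk. "NRS pain scores will be assessed hourly for 6 h after surgery, then daily for 3 days", and "the area under the curve of the NRS pain scores will be calculated using the trapezoidal method". The arms are then compared by Student's t-test at a two-sided 0.05 level.
- **Safety assessment** commits to recording every adverse event that occurs during the trial and to analysing all of them at the end. It also says: "If any severe adverse event occurs, we will terminate the EA or SEA treatment".

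The Intervention protocol section asks for the reason for any dropout to be recorded. No section provides for outcome assessment after treatment has stopped.

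**The concern.** An intention-to-treat analysis needs outcomes from everyone randomised, whether or not they kept to treatment. Here the protocol creates the gap itself. Once a participant meets the trigger, the remaining pain scores are never taken, and the analysis must fill them in.

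The trigger is tied to things that may be related to the outcome. Side effects are named, and any other reason counts too. The arms also differ in what could cause a stop. In the EA arm the needles penetrate, are manipulated to a needling sensation and carry current; in the sham arm they do neither and carry none. The harms listed under Safety assessment (bruising, haematoma, infection, pain) are therefore more plausible with EA. If those who stop have different later pain from those who continue, in a way their earlier scores do not explain, imputation under a missing-at-random assumption gives a biased comparison.

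Safety is affected as well. An event that begins after a stop falls under two incompatible instructions: collect nothing further, and record every event. The article hypothesises that EA is safe as well as effective, so this is not a side issue.

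**Working it through.** **1. The plan's own figure.** Sample size gives a base of 12 (read here as per arm) and 20% dropout. 12 / (1 − 0.20) = 15 per arm, and 2 × 15 = 30. This reproduces the stated size. The dropout allowance is 0.20 × 15 = 3 participants per arm. No power calculation is given, so there is none to check.

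**2. How much of the primary outcome a stop removes.** The schedule is hourly to 6 h, then daily for 3 days. The clock times of the daily scores are not given; I assume 24, 48 and 72 h. From the 1 h score to the 72 h score the window is 71 h. (Table 1 also lists a score upon recovery. Including it as time zero makes the window 72 h but does not change the weights in step 3.)

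- Stop after 6 h: (72 − 6) / 71 = 93% of the window is unobserved.
- Stop after 24 h: (72 − 24) / 71 = 68%.
- Stop after 48 h: (72 − 48) / 71 = 34%.

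**3. Trapezoid weights of the missing scores.** Each score is weighted by half the interval on either side.

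- 24 h score: (18 + 24) / 2 = 21 h
- 48 h score: (24 + 24) / 2 = 24 h
- 72 h score: 24 / 2 = 12 h

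The missing weight W is therefore 21 + 24 + 12 = 57 h after a 6 h stop, 24 + 12 = 36 h after a 24 h stop, and 12 h after a 48 h stop.

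**4. Bias in the AUC difference.** Let a fraction p of an arm stop, with true later scores d points above the imputed ones. For a common stopping time, the absolute bias in the difference between arms is |p_EA × d_EA − p_SEA × d_SEA| × W. Assume 3 of 15 stop in the EA arm (p = 0.20), none in the sham arm, and d from 1 to 3. Both p by arm and d are assumptions; the document gives neither.

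| Stop after | W (h) | 0.20 × W × d, d = 1 to 3 (NRS-hours) | Divided by 71 h (NRS points) |
|---|---|---|---|
| 6 h score | 57 | 11.4 to 34.2 | 0.16 to 0.48 |
| 24 h score | 36 | 7.2 to 21.6 | 0.10 to 0.30 |
| 48 h score | 12 | 2.4 to 7.2 | 0.03 to 0.10 |

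**5. Dependence on the imbalance.** With 3 stopping in EA and 1 in sham after 6 h, and the same d in both, the figure is (3 − 1) / 15 × 57 = 7.6 NRS-hours per point of d. With 3 in each arm and the same d it is zero. With 3 in sham and none in EA the sizes in the table apply with the opposite sign.

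**The case against.** The strongest reply is that the plan already has an answer. Statistical analysis pairs intention-to-treat with multiple imputation, and the rule stops further collection without discarding scores already taken. All 30 participants can be analysed in their assigned arms. This stands. A reader might infer that intention-to-treat becomes impossible, and the document does not support that. What is lost is the observed outcome after a stop, so the result rests on an imputation assumption that cannot be tested.

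Other limits also stand:

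- **Trigger.** A reader might take the rule to apply at the first deviation. It applies when a participant cannot be managed per protocol, which is broad and loosely worded but narrower. A late session or a bruise need not meet it.
- **Informative missingness.** It is tempting to treat this as fact, and as favouring EA. The document gives no reasons or rates by arm. Nothing links stopping for needling effects to higher postoperative pain, and sham participants might stop because their pain is poorly controlled. Imputation can also use a participant's own earlier scores.
- **Safety.** A reader might conclude that safety recording ends when a side effect occurs. The Safety assessment section requires the event itself to be recorded in full, with vital signs and, after a severe event, a judgement of relatedness. The conflict concerns events that arise after the stop.
- **Size.** A bias of 14 to 43 NRS-hours (0.20 × 72 × 1 to 3) would need all three EA participants to stop before any postoperative score. The 20% is also a general allowance and may include consent withdrawals, which no change to this rule would recover.
- **Stage.** This is a 30-patient pilot without a power calculation, so a biased efficacy estimate does less harm than in a confirmatory trial.

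The reply does not remove the conflict. The rule is explicit, so it is not a matter left to an unseen analysis plan. The pilot still tests efficacy at 0.05 and is meant to inform a full-scale trial.

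**Conclusion.** The concern holds as a contradiction in the protocol and a real, avoidable risk of bias. The rule undermines the intention-to-treat analysis and conflicts with the adverse event commitment for events after a stop. Multiple imputation under missing at random may not repair the loss.

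The illustrative bias in the AUC difference is about 11 to 34 NRS-hours for stops after the 6 h score, 7 to 22 after 24 h and 2 to 7 after 48 h. These figures rest on assumed assessment times, on 3 of 15 stopping in the EA arm only, and on an assumed shift of 1 to 3 points. They show what could happen and are not an estimate of what will. The direction of bias is not established.

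The point should be settled before recruitment, because scores that were never taken cannot be recovered in the analysis.

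**What to change.** Replace the sentence in Outcome measures with:

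*Participants who stop EA/SEA, or who can no longer be managed as the protocol requires, remain in the trial. NRS, HR/BP, sleep, QoR-15, SF-36 and adverse events continue to be collected as scheduled unless consent to data collection is withdrawn.*

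Analyse all participants as randomised, and keep multiple imputation for data that could not be obtained. A sensitivity analysis that shifts the imputed scores away from missing at random would show how far the result depends on that assumption.

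The cost is a few extra ratings in patients already on the ward, whose vital signs Table 1 schedules daily until discharge. The sample size stays at 15 per arm, 30 in total. The change concerns data collection only and leaves every rule on stopping treatment as it is. The consent form is not shown, so whether it needs matching wording should be checked.
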